##### Safety

For safety analysis, all non-serious and serious adverse events (SAE) are grouped according to a pre-specified side-effect coding system and tabulated. The number (and percentage) of patients experiencing any adverse event, any SAE, and any drug-related SAE are compared between treatment groups using Fisher's exact test. Safety is analyzed using the all-patients-treated approach.

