#### Primary endpoint

There are two primary end points:**Treatment Failure** (TF) (PCR adjusted) at day 63 defined according to the WHO criteria [14] as the sum of early and late treatment failures. Early Treatment Failure (ETF) could be one of the following: Development of danger signs or severe malaria on Day 0, Day 1, Day 2 or Day 3, in the presence of parasitaemia; Parasite density on Day 2 > Day 0 count, irrespective of axillary temperature; Presence of parasitaemia on Day 3 with fever (axillary temperature ≥ 37.5°C); Parasitaemia on Day 3 ≥ 25% of count on Day 0. Late treatment failure (LTF) is divided in late clinical and late parasitological failure. Late Clinical Failure (LCF): Development of danger signs or severe malaria on any day after Day 3 in the presence of parasitaemia, without previously meeting any of the criteria of Early Treatment Failure; Presence of parasitaemia and fever on any day after Day 3, without having previously meet the criteria of ETF. Late Parasitological Failure (LPF): Presence of parasitaemia on any day from day 7 onwards and axillary temperature <37.5°C, without previously meeting any of the criteria of ETF or LCF. The Adequate Clinical and Parasitological Response (ACPR) is 1-TF. It is defined as absence of parasitaemia at the end of the follow up period, irrespective of axillary temperature without previously meeting any of the criteria of early and late treatment failure. In the adjusted estimates, patients with late asexual parasite reappearance (with or without fever) are considered ACPR if the PCR analysis shows a new infection rather than a recrudescence.**Safety profiles** including significant changes in relevant laboratory values. Subjects are monitored for 63 days for possible development of adverse events. All adverse events are recorded on the specific form in the electronic CRF. Vital signs, blood chemistry and haematology are monitored and changes in relevant laboratory parameters are assessed.

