#### Secondary endpoints

PCR unadjusted treatment failure up to day 63 (TF63U); Time to treatment failure (PCR adjusted and unadjusted) during 63 days of active follow-up after treatment; Asexual parasite clearance time (PCT): Asexual parasite clearance time is defined as the time (in days) from time of randomization to 2 consecutive negative blood slides (collected at different days) - the time to the event is taken as the time to the first negative slide; Gametocytaemia (prevalence and density) at day 7, 14, 21, 28 and 63 after treatment; Hb changes day 14, 28, 42 and 63; Acute, chronic or past infection of the placenta (prevalence); Mean birth weight and prevalence of low birth weight.

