#### Patients follow up

Scheduled visits are at day 3, 7 and then every week until day 63 post-treatment. However, women are encouraged to attend the antenatal clinic if they felt ill between scheduled visits. At the end of the active follow-up period, women are asked to attend the antenatal clinic monthly and at any time they feel unhealthy until delivery. At each visit, scheduled and unscheduled, the medical history since the last visit (including any treatment taken), current signs and symptoms (if any) are collected. A blood sample for thick and thin blood film and later genotyping to determine the rate of re-infection is collected and the body temperature checked. Haematology (Hb, total white blood cell count, differential count) is measured at day 7, 14, 28 and 63; biochemistry (total bilirubin, ALAT and creatinine) at day 7 and 14.

If pregnant women recruited during the third trimester deliver before the end of the 63-day active follow, scheduled visits continue after delivery until the day 63 is completed. The outcome of pregnancy, including any congenital abnormality, the birth weight and maternal Hb are collected as soon as possible after delivery. In addition, a placenta impression smear and a placenta biopsy for later histopathological analysis are collected. Both the mother and the new-born are reassessed twice after delivery for any adverse event: between 4 and 6 weeks and then after one year (Table 3). Antimalarials or antibiotics with antimalarial activity (erythromycin or other macrolides, co-trimoxazole or other sulphonamides, any tetracycline including doxycycline, and quinolones, clindamycin) cannot be administered during the active follow up as it would lead to withdrawal of the patient from the study.

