##### History of amendments to the study protocol

Several amendments (Table 4) have been made to this study protocol based on emerging information and were approved by the relevant ethical committees. Before study start the ASAQ manufacturer provided information regarding potential transitory increase of ALAT at day 28 post-treatment. Therefore, ALAT measurement at day 28 was introduced. In addition, an overview of the reproductive toxicity of DHAPQ and mefloquine was made available by the manufacturer and showed in the animal model prolonged length of gestation and dystocic pup expulsion in animals treated close to delivery. It was therefore, decided to modified the original inclusion criterion of gestation ≥16 weeks to gestation ≥16 weeks and <37 weeks.

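### Safety is a primary endpoint, but arms are compared only on three composites without centre adjustment; pregnancy loss, neonatal death, congenital anomaly and gestation length have no stated comparison of their own

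*Protocol article*

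**What the plan says.** **Endpoints.** Under Primary endpoint, the second of two primary endpoints is the safety profile, described as laboratory changes and adverse events: "Subjects are monitored for 63 days for possible development of adverse events". The Statistical analysis section instead runs safety to one year after delivery. Under Secondary endpoints, the only outcomes tied to pregnancy or birth are these: "Acute, chronic or past infection of the placenta (prevalence); Mean birth weight and prevalence of low birth weight".

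**Comparison.** In the Safety analysis section, AEs and SAEs are "grouped according to a pre-specified side-effect coding system and tabulated". The stated between-arm comparison is of "patients experiencing any adverse event, any SAE, and any drug-related SAE are compared between treatment groups", made "using Fisher's exact test". No adjustment for centre is mentioned there, whereas the Efficacy section adjusts the primary comparison for centre.

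**Data.** Patients follow up says: "The outcome of pregnancy, including any congenital abnormality, the birth weight and maternal Hb are collected as soon as possible after delivery". Mother and newborn are reassessed at 4-6 weeks and at one year.

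**Harms the document itself names.** The Background gives fear of teratogenic and embryotoxic effects as the reason pregnant women are left out of antimalarial trials. The amendment history reports, for DHA-PQ and mefloquine, an animal signal of "prolonged length of gestation and dystocic pup expulsion in animals treated close to delivery".

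**SAE definition.** Safety variables lists congenital anomaly among the SAE criteria. It does not list miscarriage or stillbirth by name.

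**The concern.** The document names specific harms to the pregnancy and collects pregnancy outcome, yet no such harm has a stated between-arm comparison. Four features combine.

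- **Dilution.** A change in one uncommon event is a small change in a composite made mostly of other events. The drug-related SAE composite does not solve this. It is a subset of any SAE, and it depends on a causality judgement by the reporting investigator in an open-label trial.
- **Entry into the composite.** Miscarriage, stillbirth and difficult delivery qualify as SAEs only through the general criteria. Gestation length is a measurement, and it enters only if someone reports it as an event.
- **Unit of count.** The comparison counts patients, so it is unclear whether an event in the newborn counts.
- **Country.** Each drug is missing from one of four countries, so a pooled Fisher test between two drugs partly compares countries.

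At stake is whether the stated analysis gives policy makers a usable between-drug estimate for the outcomes that most concern them.

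**Working it through.** **1. The plan's own figures.**

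Sample size: 700 / (1 - 0.20) = 875, against 870 stated. For pair-wise equivalence at n = 700, true rates 95%, margin 5% and incomplete-block efficiency 8/9: SE = sqrt[2 x 0.95 x 0.05 / (700 x 8/9)] = 0.01236. Power = 2 x Phi(0.05/0.01236 - 1.96) - 1 = 96%, against 95% stated. A simulation of the additive four-centre model gave 84% for all six pairs, against 80% stated. The design is reproduced.

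The safety statement (90% power for major adverse events at 2-3%) gives no comparator.
- Read as seeing at least one event, 870 women reach 90% at 1 - 0.1^(1/870) = 0.26%, and 3480 women at 0.07%. Neither fits 2-3%.
- Read as an absolute difference between two arms of 870, 90% power needs 1% vs 3.2%, 2% vs 4.8% or 3% vs 6.3%. These are gaps of 2.2 to 3.3 points, which does fit.

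On that reading the statement concerns an event compared in its own right.

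**2. Dilution inside the composites.**

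Inputs: 870 per arm (Sample size section; the Safety section uses all treated patients) and Fisher's exact test (Safety section). Two-sided 5% is assumed. The document gives no rates for pregnancy events, other SAEs or other AEs, so all rates are assumptions. Let q be the event rate, doubling to 2q, and o the rate of other events, assumed independent:

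composite = 1 - (1 - o)(1 - q), against 1 - (1 - o)(1 - 2q).

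For q = 3% and o = 5%: 7.85% vs 10.70%. For q = 3% and o = 20%: 22.4% vs 24.8%.

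| Event | Alone | Inside any SAE (o = 5% to 20%) | Inside any AE (o = 50% to 70%) |
|---|---|---|---|
| 3% to 6% | 84% | 51% to 20% | 9% to 6% |
| 2% to 4% | 65% | 29% to 11% | 6% to 5% |
| 1% to 2% | 33% | 11% to 6% | 4% to 3% |
| 0.5% to 1% | 15% | 6% to 5% | 3% |

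The first two power columns are exact Fisher power. The last is a normal approximation counting only rejections in the direction of harm.

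Check by normal approximation, power = Phi(d/SE - 1.96):
- 3% vs 6%: SE = sqrt[(0.03 x 0.97 + 0.06 x 0.94)/870] = 0.00991, so Phi(3.03 - 1.96) = 86%.
- If the extra 3 points do not overlap with other SAEs: 10% vs 13% gives 50% and 15% vs 18% gives 39%. Both lie within the 20-51% range.
- With 870 x 0.8 = 696 per arm, 3% to 6% gives 74% alone and 42% down to 17% inside any SAE.

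**3. Country.**

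Table 1 puts each drug in three countries with 290 women each. AL is absent from Ghana, AQAS from Zambia, MQAS from Malawi and DHA-PQ from Burkina Faso. Any two drugs share two countries and differ in the third, so 290/870 = one third of each arm comes from a country the other lacks. With no drug effect, a pooled difference is shifted by one third of the difference in background rates between the two unshared countries.

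Adjustment costs some precision. At efficiency 8/9, the 86% becomes Phi(3.03 x sqrt(8/9) - 1.96) = about 81%.

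**4. What an interval would show.**

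Centre-adjusted 95% half-widths are about 1.96 x SE x sqrt(9/8):
- 3% vs 6%: 1.96 x 0.00991 x 1.06 = 2.1 points.
- 1% vs 2%: SE = 0.00582, giving 1.2 points.

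For the rarer event a test is weak, but the interval still bounds the harm.

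**The case against.** The strongest reply is that this article condenses a fuller protocol and that a detailed analysis plan is promised. Which coded terms receive their own comparison is often settled there, and the Safety section does not say that its three comparisons are the only ones. Events are also tabulated by code. Every SAE goes to a DSMB that includes a gynaecologist and a paediatrician and meets quarterly during recruitment. Miscarriage, stillbirth and neonatal death can enter through the general SAE criteria.

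Much of this stands, and it rules out several stronger readings that a reader might infer:

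- **That these outcomes will never be compared, or that a doubling would go unseen.** The document does not show this. Tables by code and the DSMB could reveal it, and the unseen plan may add comparisons.
- **That the trial exists to check these harms.** The stated safety objective is tolerability and adverse-event incidence to one year post-partum. Teratogenicity is cited as why trials in general exclude pregnancy, and the sensitive window is put at weeks 2-6 while enrolment starts at week 16. The gestation and delivery signal came by amendment and was met by an eligibility limit.
- **That the limit of under 37 weeks goes unchecked.** No analysis of this trial could check it, because later gestations are not enrolled.
- **That naming the outcomes restores power.** It does not for events near or below 1% (15-33% alone).

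What the reply does not answer is that the endpoint lists and the stated comparisons are fixed in this document. They omit these outcomes, and the stated test ignores centre in a design where country and drug are partly confounded.

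**Conclusion.** The point holds as a weakness in the stated method, not as an internal contradiction. Pregnancy loss, neonatal death, congenital anomaly and gestation length are not named endpoints and reach a stated comparison only, if at all, inside composites. For a doubling from 3% to 6% with 870 per arm, power falls from about 84-86% alone to about 20-51% inside any SAE and under 10% inside any AE. These figures rest on assumed event rates, on assumed background rates of 5-20% (SAE) and 50-70% (AE), and on a two-sided 5% level. Lower rates weaken both routes, so the case rests on separate estimates with intervals more than on separate tests. The missing centre adjustment is a defect whatever the rates. The change should be made: it is cheap, and the design already supplies the model.

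**What to change.** Add to the Safety analysis section named between-arm estimates with 95% confidence intervals, adjusted for centre as in the Efficacy section, for:

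- pregnancy loss (miscarriage or stillbirth);
- neonatal death;
- congenital anomaly;
- gestational age at delivery, with preterm and post-term proportions, noting that fundal-height dating makes these imprecise.

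Any subgrouping should be by gestation at enrolment. The interval from treatment to delivery should not be used. It arises after randomisation and is part of the outcome, since gestation at delivery is enrolment gestation plus that interval, so stratifying on it would hide any prolongation.

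Report delivery complications where they are recorded as AEs or SAEs; the follow-up section and visit schedule do not list them as a separate data item. State that miscarriage and stillbirth count as SAEs. Count maternal and offspring events separately, each with its own denominator.

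**Cost.** This is mainly analysis and definition wording, because pregnancy outcome and congenital abnormality are collected at delivery and gestation is assessed at enrolment. There will be more safety contrasts (six drug pairs for each outcome), to be read as estimates with intervals and not as confirmatory tests. Centre adjustment costs a little precision (about 86% to 81% power in the 3% vs 6% example).

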### Trial objectives and purpose

The main objective of the trial is to determine the safety and efficacy of 4 ACTs when administered to pregnant women with *P. falciparum* infection during the second and the third trimester, and collect explanatory variables for therapeutic response. The primary hypothesis is the clinical equivalence (pair-wise non-inferiority) of the 4 treatment regimens, with clinical equivalence defined as difference in treatment failure rates (PCR corrected) of 5% or less.

Specific objectives are:

to compare the efficacy of AL, AQ-AS, MQ-AS and DHA-PQ in terms of treatment failure by 63 days after start of treatment with or without genotyping; Parasite clearance time; Haematological recovery by 14, 28, 42 and 63 days post-treatment and at delivery; Birth weight measured within 72 hours of delivery; and prevalence of placenta *P. falciparum* malaria;to describe the safety profile of AL, AQ-AS, MQ-AS and DHA-PQ in terms of tolerability; incidence of adverse events until one year post-partum;to determine the relation between drug pharmacokinetics (Day 7 levels of the partner drug) and response to treatment;to assess the *in vitro* susceptibility of *P. falciparum* isolates collected before treatment to several drugs, including the partner drug tested, and to correlate their IC_50_ to treatment response.

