#### Sample size

The sample size for this study was determined by simulation with the following assumptions and requirements: (1) study conclusions are determined by two-sided 95% confidence intervals for difference in response rates (% of therapeutic success), with decision rule as described below, (2) all 4 treatments have identical true response rates of 95%, (3) 95% power for each of the 6 pair-wise comparisons and 80% power for the combined hypothesis that all treatments are therapeutically equivalent is required. With these assumptions, approximately 700 patients/treatment arm are needed. If the true response rate for one of the treatments is lower than 95%, then power is reduced to 80% (for a true response rate of 94%) or 50% (for a true response rate of 93%). Allowing for a 20% loss to follow-up, a total of 870 patients are recruited to each treatment; this is equivalent to 290 patients in each treatment group in each centre (i.e. a total centre sample size of 870 patients) – and hence a total study sample size of 3480 patients. Inclusion of HIV-infected women is not expected to have a major influence on the sample size calculation. The percentage of therapeutic success may be slightly but not dramatically lower in this subgroup of patients.

For safety, when combined, the trial is able to detect with 90% power major adverse events occurring at the frequency of at least 2-3%.

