#### Statistical analysis

A detailed analysis plan is drawn up prior to the analysis.**Baseline comparability**: Patients in each treatment group in each site are described separately with respect to baseline characteristics. The clinical importance of any imbalance will be noted, though statistical tests of significance are not undertaken.**Primary analyses**: The primary analysis of the study is the assessment of therapeutic equivalence of the 4 treatments (clinical non-inferiority) with respect to therapeutic success at day 63 and their safety throughout the follow-up, i.e. up to one year after delivery.

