##### Efficacy

Therapeutic equivalence is assessed using the pair-wise difference in response rates (percentage of women with therapeutic success). Assessment of the difference in true response rates is performed by calculating the two-sided 95% confidence interval for the difference in response rates from the observed data, using the following decision rule:

if the two-sided 95% confidence interval for the difference in response rates lies entirely between −5% and +5%, then therapeutic equivalence of the two treatments is concluded;if the 95% confidence interval for the difference in response rates includes −5% or +5%, then therapeutic equivalence cannot be established;if the 95% confidence interval for the difference in response rates lies entirely below −5% or entirely above 5%, then one treatment is clinically inferior to the other.

The primary analysis uses the combined data from all 4 centres together, with adjustment for any centre effects, using an additive model for the response rates (i.e. a generalized linear model with Bernoulli error distribution and an identity link function). This allows the assessment of all 6 possible pair-wise treatment comparisons using all available data. Equivalence will be established using two-sided confidence intervals. Though 6 treatment comparisons will be performed, no adjustment for multiplicity is needed as the focus of the study is on the individual pair-wise treatment comparisons. In addition, combined hypotheses of interest (e.g. all 4 treatments are therapeutically equivalent) require each of the individual hypotheses to be accepted. Consequently, there is no inflation of the type I error rate due to multiple testing. However, the power for combined hypotheses is lower than for the individual pair-wise comparisons. Thus, the power calculation of this study required a high (95%) power for individual pair-wise treatment comparisons, resulting in an acceptable (80%) power for the combined hypothesis. For the efficacy analysis, both an intention-to-treat and a per-protocol approach are adopted, with the per-protocol analysis being the primary approach, as recommended for equivalence studies.

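### Safety stands inside the primary equivalence assessment, but the only comparative safety method stated is Fisher's exact test, which cannot show comparability; the objectives define equivalence on treatment failure alone

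*Protocol article*

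**What the plan says.** All references are to the protocol article.

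- **Primary endpoint:** "There are two primary end points", namely PCR-adjusted treatment failure at day 63 and safety profiles.
- **Statistical analysis** (and, in nearly the same words, **Study design**): the primary analysis assesses therapeutic equivalence of the four treatments, glossed as clinical non-inferiority, "with respect to therapeutic success at day 63 and their safety throughout the follow-up, i.e. up to one year after delivery".
- **Efficacy:** the rule is based on an interval: "if the two-sided 95% confidence interval for the difference in response rates lies entirely between −5% and +5%, then therapeutic equivalence" is concluded. An interval that includes either limit means equivalence is not established. The model is additive and adjusts for centre.
- **Safety:** coded events are tabulated with numbers and percentages. For the comparison, the proportions with any AE, "any SAE, and any drug-related SAE are compared between treatment groups using Fisher's exact test". On the analysis set: "Safety is analyzed using the all-patients-treated approach".
- **Trial objectives and purpose:** clinical equivalence is defined as a "difference in treatment failure rates (PCR corrected) of 5% or less". The safety objective is worded as description.
- **Sample size:** "a total of 870 patients are recruited to each treatment". On safety, "the trial is able to detect with 90% power major adverse events occurring at the frequency of at least 2-3" per cent.

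**The concern.** An aim of equivalence or non-inferiority needs a statement of how large a difference the data rule out. A test of no difference does not give one. If p is small, a difference has been shown. If p is not small, the arms may be alike or the data may be too few to tell.

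The efficacy rule separates these two cases, because an imprecise estimate ends as equivalence not established. The safety section has no counterpart, so imprecision shows up only as non-significance. The trial is meant to identify treatments suitable in pregnancy and to inform policy. A reader given only a Fisher p-value would not see what excess of serious events remains compatible with the data.

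The article is also inconsistent about its aim. The objectives keep equivalence to treatment failure, while the primary-analysis sentence can be read to extend it to safety.

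**Working it through.** **Inputs.** From the article: 870 women recruited per treatment; safety analysed in all treated patients; four centres with three of the four arms each (Table 1). Assumed, because not stated: event rates, a two-sided 5% level, and pairwise comparison.

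**1. The article's own safety figure (90% power at 2-3%).** No comparator rate is named, so the figure has no unique reproduction.
- Read as the chance of seeing at least one event, 1 − (1 − p)^n: 90% needs n = ln 0.1 / ln 0.98 = 114 women at 2%, or ln 0.1 / ln 0.97 = 76 at 3%. With 870 women, 90% is already reached at p = 1 − 0.1^(1/870) = 0.26%.
- Read as Fisher's test, 870 vs 870: 90% is reached only if the other arm's rate is at most about 0.34% (against 2%) or 0.84% (against 3%), a ratio of about 6 (2/0.34) or 3.6 (3/0.84).

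On neither reading does the figure show that smaller excesses would be found.

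**2. Exact power of Fisher's test, 870 vs 870.** Power = Σ Bin(x; 870, p1) · Bin(y; 870, p2) over all pairs (x, y) with Fisher p ≤ 0.05.

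| Assumed rates | Power | Missed |
|---|---|---|
| 1% vs 2% | 33% | 67% |
| 2% vs 4% | 65% | 35% |
| 5% vs 7.5% | 54% | 46% |
| 3% vs 6% | 84% | 16% |
| 5% vs 10% | 98% | 2% |

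**3. What a p-value alone hides.** Take 9 vs 18 women with an SAE, of 870 each. The rates are 1.03% and 2.07%, and the difference is 9/870 = 1.03 points. Fisher p = 0.12. The 95% interval for the difference (Newcombe) is −0.2 to +2.3 points. The risk ratio is 2.0, with upper limit exp(ln 2 + 1.96·√(1/9 + 1/18 − 2/870)) = 4.4.

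**4. What an interval would deliver.** With equal rates p, the 95% half-width is 1.96·√(2p(1 − p)/870). Each centre omits one arm, so the comparison should adjust for centre. For 4 treatments, 3 per centre, 3 centres per treatment and 2 centres per pair, the design efficiency is (2 × 4)/(3 × 3) = 8/9. The variance rises by 9/8 and the half-width by √(9/8) = 1.061.

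| Rate in both arms | Unadjusted (points) | Centre-adjusted (points) |
|---|---|---|
| 1% | ±0.94 | ±0.99 |
| 2% | ±1.32 | ±1.40 |
| 3% | ±1.60 | ±1.70 |
| 5% | ±2.05 | ±2.17 |

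Using only the two centres that hold both arms gives 580 per arm, and at 5% the half-width is 2.05 × √(870/580) = ±2.51.

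**The case against.** The strongest reply is that the article does not claim equivalence on safety. The primary-analysis sentence can be read as two tasks: assess equivalence on success, and assess safety. The objectives support this reading, and the sample-size section speaks of detecting adverse events, for which a difference test is suitable. A primary endpoint need not carry an equivalence claim. This reply stands in part: the sentence is ambiguous. But the sentence does put safety in the equivalence assessment on its plain wording, so it needs correcting on either reading.

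A reader might also infer that the trial will take p > 0.05 as proof of comparable safety. The article never says so and gives no decision rule for safety. The risk follows from what is left open, not from a stated rule.

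A reader might infer that Fisher's test generally misses relevant harm. It does not: 3% vs 6% and 5% vs 10% are detected well. Low power at rare event rates comes from the sample size, and an interval would show that uncertainty without removing it.

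Intervals could appear in an analysis plan that is not shown, and their absence from an article is no fault by itself. What remains is that the article names a method that does not fit the aim it states. Finally, Fisher's test is not the only look at safety: events are tabulated, laboratory changes are assessed, and an independent board reviews the safety data. None of these is a comparative statement of how much excess harm is excluded.

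**Conclusion.** The point holds as a mismatch between stated aim and stated method, with an inconsistency between the objectives and the primary-analysis sentence. It should be corrected, but it does not invalidate the trial.

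Its size depends on event rates that the article does not give. On the assumed rates, between about a third and two thirds of the moderate excesses examined would be missed (1% vs 2%, 2% vs 4%, 5% vs 7.5%), while the larger ones mostly would not. The figures also assume a two-sided 5% level, pairwise testing and all 870 women per arm in the analysis.

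The documents do not support going further and calling the lack of a safety margin a defect. The only margin is tied to treatment failure and nothing requires one for safety. Data collection is already reported complete in this open-label trial, so a margin chosen now would be a late choice.

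**What to change.** 1. **Safety section.** For each of the six pairs, report the centre-adjusted risk difference with a two-sided 95% confidence interval for any AE, any SAE and any drug-related SAE. Use the additive model already specified for efficacy, or a risk difference stratified by centre over the centres that have both arms. The second option is a useful fallback if the identity-link model does not converge for rare events. Keep Fisher p-values as supporting only.
2. **Interpretation.** State for each pair the largest excess not ruled out, and say that non-significance is not evidence of equal safety.
3. **Study design and Statistical analysis.** Reconcile the primary-analysis sentence with the objectives by taking safety out of the equivalence wording, unless a safety margin is stated in advance. No margin is required.

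Cost: wording changes and a few more table columns, with no new data or patients. Safety conclusions become more cautious: at a 5% event rate the interval is about ±2.1 points before centre adjustment and about ±2.2 after it, so smaller excesses cannot be excluded.

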### Trial design

#### Study design

This is a non-inferiority, multicentre, randomized, open label study on 4 antimalarial treatments, namely DHA-PQ, MQAS, AQAS and AL, assessed in each site using a “balanced incomplete block design” – with 3 out of 4 arms used in each site. There are 7 sites in the study distributed in the four countries, i.e. Burkina Faso (Nanoro and Nazoanga), Ghana (Effiduase, Ejisu and Juaben), Malawi (Chikwawa) and Zambia (Nchelenge).

The treatments tested are distributed in a way to allow a head-to-head comparison and the establishment of the treatment’s relative value according to a series of outcomes (Table 1). This approach has the advantage of testing several treatment options at the same time, maximizing the use of resources, and is the most likely to achieve our aim of identifying at least 2 antimalarial treatments suitable for use in pregnancy and one rescue/alternative treatment.

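### The primary safety comparison uses an unadjusted Fisher test although each drug is absent from a different country, so country differences in event rates can appear as drug effects

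*Protocol article*

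**What the plan says.** The Primary endpoint section states that "There are two primary end points", the second being the safety profile. The Statistical analysis section makes safety part of the primary analysis, which assesses the four treatments "with respect to therapeutic success at day 63 and their safety throughout the follow-up, i.e. up to one year after delivery".

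The Safety paragraph then names the method. The numbers of patients with any adverse event, "any SAE, and any drug-related SAE are compared between treatment groups using" Fisher's exact test. On the population it says: "Safety is analyzed using the all-patients-treated approach". It mentions no stratification, no centre term and no restriction to countries that share a pair of drugs. The Sample size section also treats safety as pooled: "For safety, when combined, the trial is able to detect with 90% power".

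The Study design section describes a balanced incomplete block design, "with 3 out of 4 arms used in each site". For efficacy, by contrast, the protocol states: "The primary analysis uses the combined data from all 4 centres together, with adjustment for any centre effects".

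**The concern.** In a multicentre trial where every arm runs at every centre, an unstratified test is at worst inefficient. Here it is biased. Randomisation makes the drugs comparable only within a country, and no two drugs were given in the same set of countries. If adverse event rates differ by country for any reason, pooling by drug carries part of that difference into the drug comparison.

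The document itself gives reasons to expect such differences. HIV testing is a study requirement only in Zambia and Malawi (Table 2). The Discussion links HIV infection to more placental malaria, and malaria with HIV to higher infant mortality. The trial is open label, and each investigator ascertains events and judges causality (Safety variables).

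The error can run either way: it can make a harmless drug look harmful or conceal a real harm. The trial is meant to inform treatment policy in pregnancy, so this matters for a primary endpoint.

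**Working it through.** **Inputs from the protocol.** Table 1 gives 290 women per drug per country:

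| Country | Drugs given | Drug absent |
|---|---|---|
| Burkina Faso | AL, AQAS, MQAS | DHA-PQ |
| Ghana | AQAS, MQAS, DHA-PQ | AL |
| Malawi | DHA-PQ, AL, AQAS | MQAS |
| Zambia | MQAS, DHA-PQ, AL | AQAS |

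Each arm has 3 × 290 = 870 women, and the total is 4 × 870 = 3480, as stated.

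**The plan's own figure.** I simulated these 12 cells with the protocol's country-adjusted identity-link model and ±5-point rule, with all true response rates at 95%. At 699 evaluable women per arm, power is about 96% per pair (protocol: 95%) and about 83% for all six pairs (protocol: 80%). The layout and the efficacy model therefore behave as the protocol says. The stated safety sensitivity (90% power at 2–3%) cannot be reproduced uniquely, because no comparator rate is given.

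**Bias formula.** Let B, G, M and Z be the event rates in Burkina Faso, Ghana, Malawi and Zambia, with no drug effect, and let S = B + G + M + Z. The crude rate in an arm is (S − rate in the country where that drug is absent)/3. For two drugs, S cancels:

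- AL − AQAS = [(S − G) − (S − Z)]/3 = (Z − G)/3
- AL − DHA-PQ = [(S − G) − (S − B)]/3 = (B − G)/3

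The other four pairs follow in the same way. The bias does not depend on sample size, so a larger trial only makes false significance more likely.

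**Worked example (assumed rates).** Any-AE 20% in three countries and 40% in Zambia:

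- AL, MQAS and DHA-PQ: (20 + 20 + 40)/3 = 26.7%
- AQAS: (20 + 20 + 20)/3 = 20.0%

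AQAS looks 6.7 points safer with no drug effect. Conversely, a true excess of 6.7 points on AQAS would be cancelled in the crude comparison.

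**False significance.** Trials were simulated with 290 per cell and no drug effect, using a two-sided pooled Fisher test at 5%. All country rates are assumptions.

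| Rates | Pairs | Pooled Fisher |
|---|---|---|
| Any AE 20%; Zambia 40% | each AQAS pair | about 90% |
| Any AE 20%; Zambia 30% | each AQAS pair | 36–39% |
| Any AE 20%; Zambia 25% | each AQAS pair | 11–13% |
| SAE 2%; Zambia 6% | each AQAS pair | 34–37% |
| SAE 3%; Zambia 6% | each AQAS pair | 16–18% |
| SAE 3%; Zambia 4% | each AQAS pair | 5–6% |
| Any AE 50%; Ghana 60% | each AL pair | about 27% |
| Any AE 50%; Ghana 70% | each AL pair | about 78% |
| SAE: B 3%, G 10%, M 5%, Z 5% | AL vs DHA-PQ | 54% |
| Equal rates everywhere | any pair | at most about 5% |

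Where only one country differs, the three pairs that do not involve the drug absent from it stay close to nominal (3–6%). Where all four differ, every pair is affected. With any-AE rates of B 50%, G 60%, M 45% and Z 40%, the crude arm rates are AL 45.0%, AQAS 51.7%, MQAS 50.0% and DHA-PQ 48.3%. AL vs AQAS is then falsely significant in 79% of trials, and at least one of the six pairs in 87%.

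**With country in the analysis.** A logistic model with treatment and country gives 4–6% per pair in the Zambia scenarios with 20%/40%, 20%/30%, 3%/6% and 2%/6%. The identity-link model with country gives 4.5–5.6%, with a mean spurious difference of about zero, in three scenarios with unequal rates.

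**The case against.** - **Pooling is inferred.** The Safety paragraph does not say in words that countries are pooled. It is nevertheless the natural reading: Fisher's test as named takes no covariate, and nothing restricts the comparison to shared countries.
- **The analysis plan is not shown and may stratify.** The authors were plainly aware of centre effects, since they adjust efficacy and describe baseline by site. But the article does not leave the safety method open. It names an unadjusted test, and a plan that stratifies would have to depart from it.
- **The size rests on assumed rates.** This stands. The protocol gives no event rates by country, and the largest figures need one country to have twice the rate of the others. With a gap of 3% against 4% the error is near nominal. For very rare events (0.2% against 0.6%) it is about 2%, because Fisher's test is conservative. Drug-related SAEs may fall in that range.
- **Much of the data is shared.** For any pair, 580 of the 870 women per arm come from the same two countries. This is true, and it is why the bias is one third of the gap rather than the whole of it.
- **No pass/fail rule hangs on the test.** The ±5% rule applies to efficacy only, and safety also rests on tabulated events, causality assessment and the DSMB. This softens the consequence of a single p-value, but it does not make a biased comparison acceptable for a primary endpoint.

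**Conclusion.** The point holds. As written, the safety comparison is confounded with country by the design itself, and the protocol removes that confounding for efficacy only. The bias follows from Table 1 by arithmetic: one third of the rate gap between the two unshared countries. Only its size is uncertain. Over the assumed rates, false significance for an affected pair runs from nominal or below, when gaps are very small or events very rare, to about 90% when one country's any-AE rate is double the rest (20% against 40%). If the four countries had equal event rates there would be no bias, but nothing in the protocol supports assuming that. The analysis should be changed before the safety results are reported.

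**What to change.** Replace the unadjusted Fisher test with a comparison that includes country, for any AE, any SAE and any drug-related SAE:

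- Use a logistic model with treatment and country. For sparse events, use exact conditional logistic regression stratified by country.
- Mantel–Haenszel risk differences stratified by country are an acceptable alternative. For each pair they draw only on the two shared countries and so set aside 290 of 870 women per arm; the model uses all four countries.
- Tabulate adverse events by arm within country, so that readers can see the country rates.

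The cost is analysis wording only. The protocol reports data collection as complete; country is known for every woman, and no new data are needed.
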